#### A3. Study design

| A3.1 Describe the study design. Where this space is inadequate, continue on a separate sheet of paper. *Do not* delete page breaks or renumber pages. | |
| --- | --- |
|  | The study follows a randomised controlled trial (RCT) design and is divided into two Phases. Phase 1 is primarily an efficacy study, conducted over 12 weeks. This study will examine three exercise prescriptions (LIIT, MVIT, HIIT). Phase 2 is an effectiveness study, will be weighted towards Maori participation and will be conducted over 6 months. The exercise prescriptions used in Phase 2 will be the most successful high prescription from Phase 1 (ie either MVIT or HIIT), compared to a standard low intensity walking programme (LIIT) .The exercise prescription for the LIIT, MVIT and HIIT will be isocaloric ie those taking part in the high intensity arm of the programme will spend less overall time undertaking their exercise programme. Participants will have an elevated BMI and will not be regular exercisers. Participants will be asked to follow an exercise prescription as part of the study but will not be asked to change their diet. Participants must be physically well enough to able to undertake walking as their main form of exercise. Each phase will have separate participants.  All three of the exercise interventions will have a walking based component. They will be conducted by exercise leaders, trained to undertake the relevant exercise programmes in a standardised manner. (These exercise leaders will be provided by CPIT and are likely to include applied exercise physiology students undertaken a supervised Practicum). The exact intensity of exercise will however be individualised ie based on the subject’s pre-study fitness levels and performance when undertaking maximal volitional exercise. Fitness will improve during the study, thus exercise load will increase as the study progresses. Some subjects in the high intensity arm may therefore be considered ‘fit’ enough to incorporate a light jogging component to their exercise plan.  Data collection for Phase 1 will be undertaken before and after the twelve week intervention period. The same data will be collected for Phase 2 but will be collected at three time points: week 0, week 13 and week 26. Data will include a standardised exercise/fitness assessment, measuring V02 max on a treadmill test, standard anthropomorphic measurements, including waist circumference and an impedance measurement of total body fat, fasting venous blood collection for measurement of insulin, glucose, lipids and HsCRP. Subjects will complete several validated questionnaires including a four day food diary (to assess the extent that change in diet might act as a confounder) and quality of life assessments. The exercise physiology researchers undertaking the primary outcome measurement (VO2 max), will be blinded to group allocation.  Trial conduct, including the reporting of subject enrolment and follow up, will be undertaken using the CONSORT (Consolidated Standards of Reporting Trials) framework.  In summary phase 1 will look to use the positive results found in laboratory based heavily structured and tightly monitored exercise interventions and transfer these positive results to more community-based, less structured but still tightly controlled exercise intervention. In Phase 2 of the study we want to use the results found in phase 1 and apply them to an even less-structured, less tightly controlled but more realistic and much less expensive community-based exercise intervention.  (see Appendix 1 on separate sheet for more detail). |

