#### A5. Statistical method

| A5.1 Is the method of analysis quantitative? | | | X | Yes |  | No |
| --- | --- | --- | --- | --- | --- | --- |
|  | | | | | | |
| Or qualitative? | | |  | Yes | X | No |
|  | | | | | | |
| If the method of analysis is **wholly qualitative**, go to question A5.4. If the method of analysis is **wholly or partly quantitative**, complete the following: | | | | | | |
|  | | | | | | |
| A5.2 Describe the statistical method that will be used to analyse the data. | | | | | | |
|  | Initial data analysis will be conducted by [name] and colleagues using the Statistical Package for the Social Sciences (SPSS) software programme. Final data analysis will be undertaken under the supervision of Associate [name], medical biostatistician. For both studies changes in continuous outcome measures (e.g. VO2max, BMI, etc) will be compared between groups using ANCOVA. These models will utilise the stratification variable, gender, as a factor and the baseline measure as a covariate. The appropriateness of these parametric analyses will be confirmed by visual inspection of the residual plots. If these do not confirm normality, data maybe transformed prior to analyses and if this does not remedy problems then non-parametric analyses will be undertaken. A two-tailed p value of <0.05 will be taken to indicate statistical significance.  The primary outcome measure is change in VO2max.  The secondary outcome measures are changes in: BMI, waist circumference, blood pressure, insulin sensitivity (HOMA) and lipids.  Tertiary outcome measures are changes in: % body fat as measured by bioimpedance, Quality of Life, hs CRP.  Samples will also be collected for an exploratory study measuring changes in a novel marker of muscular ‘fitness’, namely monocyte mitochondrial load. | | | | | |
|  | | | | | | |
| A5.3 Has specialist statistical advice been obtained about this study? | | | X | Yes |  | No |
|  | | | | | | |
| If **yes**, from whom? (A brief statistical report should be included if appropriate.) | | Associate [name], University of Otago. | | | | |
|  | | | | | | |
| A5.4 If the method of analysis is **wholly or partly qualitative**, specify the method. Why is this method appropriate? If interviews are to be used, include the general areas around which they will be based and a copy of the interview guide, if one is to be used. Copies of any questionnaires that will be used must be included. | | | | | | |
|  | Not applicable | | | | | |

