|  | Venesection will be undertaken by trained researchers, including research nurses. Collection of anthropometric measurements will be undertaken by all researchers, under the supervision of [name], who is Level II accredited with the **International Society for the Advancement of Kinanthropometry (ISAK).**  Clinical assessments will be undertaken by the research nurses, under the supervision of [name] and also directly by [name]. [name] will be responsible for screening potential subjects’ medical fitness to participate in the project, in conjunction with a report from the subject’s General Practitioner, as required.  Exercise testing (ie measurement of V02max) will be undertaken by trained exercise physiology researchers – [name], [name], [name], [name]. The exercise interventions will be supervised either directly by these exercise physiologists, or indirectly through supervision of exercise physiology students, who will undertake the assessment. | | | | | | | | | | | |
|  | | | | | | | | | | | | |
| B3. What other research studies is the lead investigator currently involved with? | | | | | | | | | | | | |
|  | [name] will have completed data collection for a three year HRC funded dietary study, by December 2009. She supervises sample collection on behalf of the Christchurch Diabetes Centre, for TrialNet, a long term multinational natural history study of antibody status of subjects at risk of type 1 diabetes. She is the Diabetes Centre site investigator for two international pharmaceutical studies of DPP IV inhibitors (an efficacy and a cardiovascular outcome study). | | | | | | | | | | | |
|  | | | | | | | | | | | | |
| B4. Where will the research procedures take place? | | | | | | | | | | | | |
|  | Fasting venous blood samples and questionnaires will collected at Christchurch Diabetes Centre.  Anthropometric and Exercise testing will take place at the Exercise Science Laboratory, University of Canterbury ([name] Campus).  Exercise training will take place in a local park (e.g. Hagley Park) | | | | | | | | | | | |
|  | | | | | | | | | | | | |
| B5. How do the research procedures differ from standard treatment procedures? | | | | | | | | | | | | |

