|  | 1. **Exercise programme.** The direct supervisors of the exercise programme will ask participants to report minor (as well as major) physical symptoms, such as musculoskeletal pains. These adverse events will then report back to the research nurse and physician ([name]). A course of action as a result of symptoms may be suggested e.g. a rest/recovery period away from exercise for minor musculoskeletal pains. Alternatively the participant may be advised to seek an opinion from their GP for more serious complains. 2. **Exercise testing.** Some subjects may suffer transient light headedness of breathlessness during maximal exercise testing. If this progresses, the exercise test will be terminated early. Participants will be observed for any adverse outcomes during the course of their exercise testing. After exercise testing participants will be monitored for at least 20 minutes. Exercise physiologists or their students will also be in regular contact with participants, as they will be supervising the regular exercise sessions. 3. **Venesection.** No major adverse events are anticipated but there may be minor bruising that will be minimised by applying pressure to the venepuncture site. Subjects with a history of vasovagal faints will be venesected lying down. | | | | | | | | | | | |
|  | | | | | | | | | | | | |
| B12. If the study is a clinical trial, are participants to be provided with a card | | | | | |  | Yes | | X | | No | |
| confirming their participation, medication and the contact phone number of the principal investigator? No, because they are not on any study medication | | | | | | | | | | | | |
|  | | | | | | | | | | | | |
| B12.1 Do you intend to inform the participant’s GP that their patient is a | | | | | | x | Yes | |  | | No | |
| participant in this study? (If yes, consent from the participant is required.) | | | | | | | | | | | | |
|  | | | | | | | | | | | | |
| B12.2 Do you intend to inform the GP of all clinically significant abnormal | | | | | | X | Yes | |  | | No | |
| results obtained during study conduct? | | | | | | | | | | | | |
|  | | | | | | | | | | | | |
| B13. Is the trial being reviewed by a data and safety monitoring board (DSMB)? | | | | | |  | Yes | | X | | No | |
|  | | | | | | | | | | | | |
| If **yes**, who is the funder of the DSMB? | | | |  | HRC |  | Sponsor | |  | | Other | |
|  | | | | | | | | | | | | |
| If **‘Other’**, please specify. | | Not applicable | | | | | | | | | | |
|  | | | | | | | | | | | | |

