**Appendix 1.**

***Research Study Design continued (from section A.3.1)***

**Phase 1 – details of exercise intervention**

The exercise interventions will be based on previously successful protocols, undertaking in the exercise physiology laboratory. In phase one, 60 participants will be randomly assigned to LIET (low intensity exercise) (N = 20), MVIT (maximal volitional intensive training) (N=20) or high intensity training (N = 20). All subjects will undergo a standardised, supervised paired maximal intensity exercise treadmill test to measure VO2max and paired blood tests, before and immediately after the 12 week intervention. The exercise intervention will be undertaken in groups of around 6 participants per group.

The three exercise prescriptions will be isocaloric ie the same overall energy expenditure will take place per session in all three groups but the method, hence time requirements to achieve this will vary. All groups will complete 3 supervised training sessions per week, based in Hagley Park. Exercise groups will be instructed by health and physical activity undergraduates from CPIT, Canterbury or Lincoln University who will all have current First Aid qualifications and will be given training and guidance on how to organise and conduct the training sessions. All participants will exercise with the aid of a heart rate monitor, thereby allowing the participants to control their corresponding exercise heart rate relative to VO2peak. The instructors will monitor each participant’s heart rate during exercise to ensure training sessions are carried out in the desired heart rate throughout the 12 week training period. As fitness improves, the exercise load ie intensity of exercise will be increased.

**High intensity exercise groups (HIITT and MVIT).** The HIIT and MVIT groups will complete a warm-up for 5 min (at an intensity of 50-60% VO2peak or 65-75% heart rate peak). The HIIT group will then walk for four intervals of 4 min at 80-90% VO2peak (85-95% heart rate peak), interspersed with 3 recovery periods of 3 min at 50-60% VO2peak. The MVIT group will exercise ‘as hard as they can’ ie at a similar intensity to the final minute of the exercise treadmill test undertaken at baseline, for 60 second intervals, followed by a cool down period then further maximal intensity exercise over the course of the session. At the end of the session, HIIT and MVIT subjects will complete a cool-down of 3 min at 50-60% VO2peak.

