**Phase 2**

In phase two, results from phase one will be used to fine-tune the testing and training protocols. In this phase 44 new to the study participants will be randomly assigned into 2 groups; the best high intensity programme from Phase (ie HIIT or MVIT) and a control group undertaking LIET. There will be 22 participants in each group. Subjects will undertake blood testing and VO2 max as for Phase one at times 0, 13 and 26 weeks. The second VO2max test done at 13 weeks will be used to check progress and adjust the training intensities for the final 3 months of training. Once a week each exercise group will come together at a local venue (Halswell Health Medical Centre or the Whanau Tautoko Charitable Trust) where instructors (trained undergraduates from CPIT, Canterbury or Lincoln University who will all have current First Aid qualifications) will take the group through their training for that day. The other two exercise sessions each week will take place at a venue chosen by the individual participants, either at the participant’s home or in a convenient community location. All participants will exercise with the aid of a heart rate monitor thereby allowing the participants to control their corresponding exercise heart rate relative to VO2peak. The instructors will monitor each participant’s heart rate each week to ensure training sessions are carried out in the desired heart rate throughout the 6 month training period

See next page for the testing protocols.

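### Section B2 lets the VO2max testers supervise the exercise sessions, so the blinding stated in A3.1 is not assured for follow-up tests

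*Protocol*

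**What the plan says.** On blinding, section A3.1 makes one unqualified statement: "The exercise physiology researchers undertaking the primary outcome measurement (VO2 max), will be blinded to group allocation". Section A5.2 fixes what is being protected: "The primary outcome measure is change in VO2max"; section A1.1 confirms that this is the primary outcome of both phases.

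On staffing, section B2 says "Exercise testing (ie measurement of V02max) will be undertaken by trained exercise physiology researchers" and lists four of them (names removed). Its next sentence reads "The exercise interventions will be supervised either directly by these exercise physiologists, or indirectly through supervision of exercise physiology students".

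On who leads the sessions, A3.1 says "These exercise leaders will be provided by CPIT and are likely to include applied exercise physiology students", and Appendix 1 says for Phase 1 "Exercise groups will be instructed by health and physical activity undergraduates from CPIT, Canterbury or Lincoln University". Appendix 1 gives a similar description of the Phase 2 instructors. Section B11, on adverse events, adds "Exercise physiologists or their students will also be in regular contact with participants, as they will be supervising the regular exercise sessions".

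**The concern.** Participants in an exercise trial know what they are doing, so concealment of the arm from the tester is the blinding that this design can offer. VO2max here comes from a maximal treadmill test. Gas analysis is objective, but how hard a participant is urged on, and when the effort is judged complete, depend partly on the person running the test. A tester who knows the arm could influence the result without intending to.

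The stake is the primary outcome of both phases. Phase 1 also decides which high-intensity programme goes into Phase 2. If that choice rests on VO2max, a distortion in Phase 1 would carry forward. A report that repeated the A3.1 sentence could also describe outcome assessment as blinded when it was not, and that cannot be repaired once the tests are done.

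**Working it through.** This is a matter of reading sections together; no figure decides it.

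1. **Who tests.** B2 assigns VO2max measurement to the four researchers it lists.
2. **Who supervises.** The next sentence of B2 refers to *these* exercise physiologists. The only exercise physiologists just mentioned are the testers, so the overlap is in the text even with names removed. There are two routes: direct supervision of sessions, or supervision of the students who run them.
3. **Whether supervising reveals the arm.** Appendix 1 describes steady walking for roughly 41 minutes (low intensity), four 4-minute intervals with recovery periods (HIIT), and repeated 60-second maximal bouts (MVIT), in groups of about 6. Nobody could watch a session without knowing which it was. Supervised sessions number 3 × 12 = 36 per participant in Phase 1 and, at one a week, about 26 in Phase 2.
4. **Which tests are exposed.** A4.3 places randomisation after baseline measurement, so baseline tests are safe. That leaves one of two tests per participant in Phase 1 and two of three (weeks 13 and 26) in Phase 2, and of these only tests where the tester has also supervised that participant's group or its student leaders.
5. **Whether anything separates the roles.** I found no statement that testers and supervisors are different people, or that supervising physiologists do not test the participants they have supervised.

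**Scale, on assumed values only.** The documents give no size for a tester effect. The plan's own Phase 1 figure reproduces: n = 2 × (1.960 + 0.842)² / 1.0² = 15.7, so 16 per arm, as in A4.2. Take its SD of 4 ml/kg/min, no true difference between two arms, and an assumed average shift b towards one arm. Then SE = 4 × √(2/n), which is 1.414 for n = 16 and 1.206 for n = 22, and the chance of p < 0.05 is 1 − Φ(1.96 − b/SE) + Φ(−1.96 − b/SE).

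| Assumed shift b (ml/kg/min) | 16 per arm | 22 per arm |
|---|---|---|
| 0 | 5% | 5% |
| 0.5 | 6.4% | 7.0% |
| 1 | 10.9% | 13.2% |
| 1.5 | 18.6% | 23.8% |
| 2 | 29.3% | 38.2% |

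If only a fraction of an arm's tests were affected, b would shrink in proportion. The table shows what such shifts would do at these sample sizes. It is not evidence that any shift would occur.

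**The case against.** The best defence is that B2 is an either/or sentence in a section on harm, whereas A3.1 is the only place that addresses blinding and does so plainly. A3.1 and Appendix 1 consistently have students or undergraduates leading the sessions. With four testers listed, a participant could be tested by someone who never saw that participant's group, and overseeing students does not by itself mean knowing each person's arm. B5 says that fitness testing follows a standardised protocol, and Appendix 1 records respiratory exchange ratio, heart rate and perceived exertion, which give some check on effort.

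Much of this stands, and it rules out several stronger readings:

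- A reader might infer that B2 abolishes blinding, or that every follow-up test is unblinded. It permits the overlap but does not require it.
- A reader might take B11 as a second statement of the overlap. It mentions exercise physiologists or their students without identifying them as the testers, so it is compatible with the overlap but does not establish it.
- A reader might infer that testers check heart rates in training. Appendix 1 gives that to the instructors.
- Appendix 1 says for Phase 2 "The second VO2max test done at 13 weeks will be used to check progress and adjust the training intensities". A reader might infer that the tester must know the arm. The text does not say who makes the adjustment; a blinded tester could report the result and someone else apply it.

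What the defence does not meet is the direct route in B2. An unqualified promise of blinding cannot stand beside a sentence that allows those same people to supervise the intervention, when nothing keeps the roles apart for a given participant.

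**Conclusion.** The point holds as an internal contradiction between A3.1 and B2 about a stated property of the primary outcome. As written, blinding of VO2max measurement is claimed but not assured for post-randomisation tests in either phase.

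This rests on reading *these* in B2 as the listed testers, which the sentence order supports, and on the arms being recognisable to anyone supervising a session, which Appendix 1 makes plain. How many tests would be affected depends on rostering that the protocol does not describe, and the size and direction of any bias cannot be derived from the documents. The sample size, endpoint and analysis are not called into question.

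**What to change.** Reconcile A3.1 and B2:

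- State in B2 that whoever conducts or scores a participant's post-randomisation VO2max test does not supervise that participant's sessions or the students leading them.
- State for Phase 2 that the week-13 result is passed to a team member who is not testing, and that this person applies it to training.
- If the existing staff cannot be rostered this way, qualify or delete the blinding statement in A3.1 so that the report does not claim more than was done.

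The rule works participant by participant, so the four listed testers can divide the roles among themselves. The cost is a wording amendment and some loss of rostering flexibility, which will be felt most on busy testing mornings (Appendix 1 allows for up to twelve tests). Baseline testing needs no change.

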|  | **Inclusion Criteria:**  Aged 35-60 years inclusive  BMI ≥28 and ≤40  Sedentary (no regular physical activity in last 3 months).  **Exclusion Criteria:**  Underlying musculoskeletal conditions that preclude subjects being able to walk briskly for up to 50 minutes  Active cardiac conditions including angina  Intermittent claudication  Underlying respiratory conditions, including asthma requiring use of an inhaler within the previous one year  Any chronic condition which, in the opinion of the potential subject’s GP or principle investigator, would make it unsafe for the subject to participate in a high intensity exercise programme (ie brisk walking)  Myopathy, including subjects on statins with moderate to severe myopathic symptoms  Active psychiatric illness  Any other chronic condition that might require a change in medication during the study (for example subjects with diabetes on sulphonylureas and insulin, subjects requiring variable doses of oral corticosteroids)  Pregnant or planning to become pregnant during the duration of the study  History of malignancy (other than skin malignancy excluding melanoma) in the previous 5 years  Treated hypertension requiring more than one antihypertensive agent  Current or recent weight change (self reported) of >5kg in last 3 months  Other reasons why taking part would be practically difficult | | | | | | | | | | | |
|  | | | | | | | | | | | | |
| B9. What are the physical or psychological risks or side effects to participants or third parties? Describe what action will be taken to minimise any such risks or side effects. | | | | | | | | | | | | |

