**Low intensity exercise group.** The LIET group will complete walking at an intensity of 50-60% for the time it will take to burn off similar calories to the HIIT and MVIT groups. (The approximate value will be ~41 min which follows previous research paradigms (Rognmo *et al*, 2004) and is based on the average VO2peak for all groups measured at baseline).

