**Baseline Testing**

About a week prior to baseline testing, consenting subjects will be sent a four day food record and instructions about completing this, the quality of life and health and exercise history questionnaires and the facilitators and barriers to change questionnaire. They will also be given instructions about undertaking an overnight fast. Subjects will bring their completed questionnaires to the first study visit.

Day -1. Arrive at Diabetes Clinic ([name]) from 7am-9am in fasted state.

Hand in completed records and questionnaires, which will be checked for completeness by the researchers. Any outstanding issues with the consent forms will be completed prior to venesection. A

fasting blood sample will be taken and anthropomorphic measurements will also be done in the fasting state. Subjects will be offered a light breakfast, as required and any outstanding paperwork will then be completed.

It is anticipated that up to 10 subjects will be screened on any given morning.

Day 0. Arrive at Canterbury University (College of Education Exercise laboratory, [name]) between 7am-10am either fasting or after a light breakfast (subject’s preference). Complete Maximal Treadmill Test.

Facilities and staff are available to undertake testing in up to twelve subjects per morning.

Days 2-14. Rest – await results of randomisation and group allocation.

Days 2-14 Start the exercise programme within a fortnight of randomisation.

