**Phase 2.**

The subjects will be randomly selected to one of 2 groups (Low intensity control group and High-intensity intervention group). The exercise prescription for these two groups will be based on the outcomes from phase 1 of the study and will be for 26 weeks rather than twelve weeks. The measurement of V02 max, fasting blood samples, questionnaires and anthropomorphic measurements will be as for Phase 1, but undertaken at 0, 13 and 26 weeks. Mitochondrial depletion studies will not be undertaken for Phase 2 (ie they will be done for Phase 1 only). The only location that will change is the location for the exercise prescription, which will now be near the subjects’ own home ie around the Aranui or Halswell area.

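### B8's catch-all medical exclusion glosses the high intensity programme as brisk walking, which gives the modality but not the intensity, and the clause leaves out the maximal treadmill test

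*Protocol*

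**What the plan says.** Section B8 lists specific exclusions (active cardiac disease, claudication, respiratory conditions, myopathy, hypertension on more than one agent and others). It also has a catch-all for any other chronic condition that the GP or investigator believes "would make it unsafe for the subject to participate in a high intensity exercise programme (ie brisk walking".

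Appendix 1 describes what entrants actually do:

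- **Testing, Phase 1.** "All subjects will undergo a standardised, supervised paired maximal intensity exercise treadmill test to measure VO2max", with paired blood tests, before and after the 12 weeks. Under Baseline Testing, the Day 0 entry is "Complete Maximal Treadmill Test".
- **Testing, Phase 2.** Measurements "will be as for Phase 1, but undertaken at 0, 13 and 26 weeks".
- **MVIT.** Maximal-effort bouts, with the level described as "similar intensity to the final minute of the exercise treadmill test undertaken at baseline, for 60 second intervals, followed by a cool down period", repeated through the session.
- **HIIT.** After a warm-up, participants "walk for four intervals of 4 min at 80-90% VO2peak (85-95% heart rate peak"), with recovery periods between.

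A3.1 says that all three interventions have a walking component and that some fitter participants in the high intensity arm may add light jogging.

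**The concern.** The catch-all is the rule for chronic conditions that the specific exclusions do not name. The person applying it is asked one question: is this programme safe for this subject? The bracket then tells that person what the programme is. If it conveys a milder demand than the protocol makes, a borderline condition may be judged against the wrong effort, and two assessors may judge it differently.

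This matters because of who enters and what they face. Entrants are sedentary, aged 35 to 60, with a BMI of 28 to 40. B9 itself recognises that taking participants to their maximum in the fitness tests could bring silent cardiovascular disease to light. What is at stake is participant safety and consistent screening, not the analysis.

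**Working it through.** The documents give no figure to reproduce and no formula applies. The check sets the criterion beside each demand that the protocol places on entrants.

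1. **What the criterion covers.** It covers the exercise programme, described first as high intensity and then equated with brisk walking. Testing is not mentioned.

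2. **HIIT (Appendix 1).** It is walked, so the gloss is right about modality. The prescribed intensity is 80-90% of VO2peak, or 85-95% of peak heart rate. Nothing in the gloss conveys that. The gloss is partly right.

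3. **MVIT (Appendix 1).** The bouts last 60 seconds, at maximal effort, at about the level reached in the last minute of a maximal treadmill test. Brisk walking does not describe this. Twenty of the 60 Phase 1 entrants are allocated to MVIT, and Phase 2 may use it if it is the better high intensity arm.

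4. **Maximal treadmill test (Appendix 1).** Every entrant takes it, including those later allocated to low intensity exercise: twice in Phase 1, three times in Phase 2 (weeks 0, 13 and 26). The clause does not describe the test too mildly; it does not cover it.

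5. **Order of events.** A4.3 places randomisation after baseline measurements, and Baseline Testing puts the treadmill test on Day 0, before allocation is known. Two things follow. When eligibility is judged, the arm is unknown, so the criterion has to fit the hardest programme an entrant might draw. But anyone who draws MVIT has already worked at about that intensity in the laboratory.

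6. **Does another section correct the wording?** B2 screens medical fitness for the project as a whole, which is wider than the programme, but the GP's report is sought only where needed. B9 uses the PAR-Q to identify higher-risk participants; a positive answer leads to closer monitoring, with no stated exclusion. Appendix 1 (Initial screening and consent) tells potential participants about exercise testing and encourages them to talk to their GP. These reduce the risk. None changes what the B8 criterion asks.

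**The case against.** The strongest reply is that the operative words are high intensity exercise programme, and that the bracket only adds the modality. A3.1 requires participants to be fit enough to walk as their main exercise, HIIT is walked, and the document uses ie loosely elsewhere: A1.1 glosses MVIT as interval training, although HIIT is interval training too. The investigator knows the interventions, and nothing says that GPs are handed the B8 text. The form asks for a brief description, and the checklist lists a separate study protocol that is not at hand. B10 puts a nurse and a defibrillator at testing, and B11 adds early termination of the test and at least 20 minutes of observation.

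Much of this stands, and it is why the point is small. It does not rescue the gloss for MVIT, and it does not bring the test within the criterion. Brevity is no defence either, since deleting the bracket would be shorter.

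Three stronger readings are tempting, and the documents do not support them.

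- **That the gap can be measured against the low intensity arm.** "The LIET group will complete walking at an intensity of 50-60" percent, so a reader might subtract that from the HIIT figure. But the protocol never equates brisk walking with the control arm's walking. It gives brisk walking no intensity, and the term appears only in B8. The subtraction compares arms, not the criterion with the demand.
- **That the musculoskeletal exclusion has the same fault.** It reads "Underlying musculoskeletal conditions that preclude subjects being able to walk briskly for up to 50 minutes". Fifty minutes matches the session ceiling in B1 and walking is the main mode of exercise. A chronic condition that makes harder effort unsafe falls to the catch-all. Changing this criterion would be preference.
- **That MVIT exposes people to an untried intensity.** The baseline test comes first. The protocol states no rule for excluding anyone on its result, but the intensity is not new to them.

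**Conclusion.** The point holds as a minor correction to safety wording. The gloss in B8 is fair on modality, silent on HIIT's intensity and wrong for MVIT; the clause omits the maximal test taken by all entrants. This is a stated eligibility rule at odds with the intervention text in the same document, not detail left for elsewhere.

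Its size cannot be computed. The documents give no event rate and no way to count participants admitted because of the wording. A reader might infer that unsuitable people will be enrolled or harmed; nothing shown supports that, given the project-level screening, the specific exclusions, the cover at testing and the test before allocation. Power, alpha and the primary comparison of change in VO2max are unaffected.

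The conclusion assumes that the B8 wording is what assessors apply. If the separate study protocol states the criterion differently, the correction is confined to this form.

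**What to change.** In B8, replace the brisk walking gloss so that the catch-all names both the test and the programme's intensity. For example: *would make it unsafe to undergo maximal treadmill testing or to take part in a high intensity exercise programme (interval exercise up to maximal volitional effort, see Appendix 1)*. Leave the musculoskeletal exclusion as it is. Which conditions then exclude a subject remains for the study's clinicians.

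The cost is one edited sentence and possibly a few more screen failures. No change to the sample size or the analysis is needed.
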